##### EEG

EEG will be recorded using standard clinical procedures including a 28-channel system and video observations within 1 h before or after fMRI (or as close to this time as possible) and read by board-certified electroencephalographers with experience in neurocritical care EEG. Artifacts such as those due to excessive muscular activity will be dealt with according to standard clinical procedures (e.g., adjustment of EEG equipment, removing sources of noise from the environment, post-processual data cleansing). We will assess EEG background activity and EEG reactivity both by visual and by spectral EEG analysis, including absolute and relative EEG power in different frequency bands. *EEG background activity:* Ten minutes of resting state EEG with the patient in a quiet environment will be analyzed; artifacts in the ICU settings such as background noise will be dealt with and prevented (if possible) according to standard clinical procedures. In addition to visual EEG analysis by board-certified electroencephalographers, 2x6 10 s artifact-free EEG segments will be compared pairwise and analyzed using EEG spectral analysis to assess for spontaneous fluctuations in the background activity (which allows us to distinguish between spontaneous fluctuations and evoked reactive EEG changes following external stimuli during subsequent reactivity testing). *Reactivity:* EEG reactivity is defined as any change in frequency or amplitude of the EEG background activity resulting from a specific external stimulus (32). However, although different methods exist to assess EEG reactivity, all those methods are poorly validated (or not at all). In a recent review, Azabou et al. analyzed more than 200 studies and concluded that current assessment methods are very heterogeneous, and that consensus for standardizations of stimulations and interpretations is absent (33). Therefore, we will use a battery of easy-to-implement stimulations and evaluate EEG reactivity both visually and using spectral EEG analysis, which will reduce interrater variability. To test EEG reactivity, we will apply auditory, sensory and nociceptive stimuli as well as eye opening. Each stimulation will be analyzed and graded for presence or absence of reactivity in the EEG background. Auditory stimulation by calling the patient by their own name has been shown to elicit a robust electrophysiological response, especially when involving a familiar voice (34). Further, we will apply nociceptive (10 s of compression of the earlobes bilaterally), sensory (light touch involving the external openings of the nostrils) and visual stimulation (passive eye opening/eye closure). All procedures will be performed by trained EEG technicians supervised by the CONNECT-ME study team. Absolute total and relative power will be evaluated in the delta (1–4 Hz), theta (4–8 Hz), alpha (8–13 Hz), beta (13–30 Hz), and gamma (>30Hz) bands and averaged within each EEG channel. For detailed analysis the electrodes will be grouped into four regions of interest: fronto-central (Fp1, Fp2, F3, F4, C3, C4), temporal (F7, F8, T7, T8, P7, P8), parieto-occipital (P3, P4, O1, O2), and midline (Fz, Cz, Pz). EEG patterns will be classified according to Synek's scale (35). In addition to conventional analyses and once a sufficient number of patients has been included (~from 50 patients onwards), we will aim for data-driven approaches as well, using machine learning paradigms, to search for EEG markers of consciousness such as recently proposed (36–38).


#### Work package 2 (clinical database, biobank)

To maximize the learning effect and to facilitate research, we will collect all relevant clinical, neurophysiological and imaging data in a comprehensive longitudinal database. This database is currently being developed, using REDCap which is provided free of charge to health care providers within the Capital Region of Denmark (45). At present, the database consists of 11 instruments (*Study ID; Cause of ICU admission; Baseline Data at ICU admission; Laboratory investigations; Neurological exam; MRI, including fMRI; EEG; Pupillometry; Neurological exam and data at ICU discharge; 3 months follow-up; and 12 months follow-up*) and at total of 555 fields (= questions). For a given patient, only a subset of these fields needs to be answered, depending on the diagnosis at admission and initial diagnostic procedures. Clinical outcome data will be assessed by a trained research nurse and a clinical PhD student, either by telephone interview or during follow up visits, using established rating scales (e.g., Coma Recovery Scale-Revised, modified Rankin Scale, Barthel index) at hospital discharge and at 3, respectively, 12 months. Target clinical data include (but are not limited to): age, sex, previous medical history (including hereditary predispositions), medication (including drugs with potential influence on consciousness levels such as antiepileptics or antidepressants), cause of admission, sedation, surgical and non-surgical complications, comprehensive laboratory investigations, neurological examination, CRS-R, GCS, FOUR, and outcome data including modified Rankin Scale (mRS), Barthel index, Glasgow Outcome Scale (GOS), as well as whether at follow-up the patient lives at home, is admitted to a rehabilitation facility, or resides in a nursing home. Neurophysiological data include (but are not limited to) resting state, passive and active EEG paradigms and (where appropriate) evoked potentials, including SSEP and BAEP. Imaging data include data from resting state, passive and active fMRI paradigms and structural MRI, including (but not limited to) T1- and T2-weighted imaging, DWI, FLAIR, gradient echo sequences and (where appropriate) MR spectroscopy and tractography. In addition, we are setting up a biobank for cerebrospinal fluid, blood and feces samples for future studies related to genomics, metabolomics and microbiomics. Minus 80° freezer facilities are available at our institution.

#### Work package 3 (passive fMRI paradigms)

We will set-up a passive fMRI paradigm using two oddball paradigms (“subject's own name” and semantic ambiguity), and we will assess patients (*n* = 12) clinically as outlined above. Active and passive paradigms will be set-up together with fMRI engineers and data analysists from the Neurobiology Research Unit, University of Copenhagen. Prior to inclusion, patients may be examined by brainstem auditory evoked potentials (BAEP) and somatosensory evoked potentials (SSEP) to ensure intact primary auditory and sensory cortex function.

#### Work package 4 (active fMRI paradigms)

We will establish an active fMRI paradigm by means of visual imagery tasks (playing tennis, navigating in a familiar surrounding) as described earlier [for review, see (1)] and a novel motor imagery task (finger tapping; opening and closing a fist) developed in-house, using a similar convenience sample (*n* = 12) as in work package 1. Patients will be clinically evaluated on a daily basis; including 60 min prior to and after each fMRI assessment, in order to capture fluctuations in consciousness levels as accurately as possible.

#### Work package 5 (clinical EEG database)

In order to correlate resting state EEG with clinical outcome data, we will assess a clinical EEG database, available at the Department of Clinical Neurophysiology, Rigshospitalet, Copenhagen University Hospital, for EEG complexity and other advanced EEG measures following acute brain injury [for review, see (1)].

#### Work package 6 (passive EEG paradigms)

We will set up passive EEG paradigms, using series of standardized behavioral testing, including central pain stimulation, sensory stimulation of the nostrils using a swab, passive eye opening, and oddball paradigms (“subject's own name,” semantic ambiguity) as described previously [for review, see (1, 32, 33, 36, 38)]. For semantic ambiguity and subject's own names, in addition to the markers of EEG complexity outlined earlier, we will aim for analysis of evoked potentials, including, but not necessarily limited to, the mismatch negativity (MMN), P300 and N400. However, as the sensitivity of the latter has been questioned recently (46), we may opt to adopt alternative EEG markers and evoked potentials as soon as they become validated in the future). Clinical evaluation of patients (*n* = 12) will be performed as described. Healthy volunteers recruited from the staff of our institution will serve as control (*n* = 12). Active and passive EEG paradigms will be set-up together with electrophysiological engineers and data analysists from the Department of Clinical Neurophysiology, Rigshospitalet, Copenhagen University Hospital. As stated earlier, patients may be examined by brainstem auditory evoked potentials (BAEP) and somatosensory evoked potentials (SSEP) to confirm primary auditory and sensory cortex integrity.

#### Work package 7 (active EEG paradigms)

Akin to the fMRI paradigm, we will establish an active EEG paradigm using motor imagery tasks (finger tapping; opening and closing a fist), as described earlier [see work package 6 for analysis of EEG markers and evoked potentials, and for review, see (1, 32, 33, 36, 38)]. Clinical evaluation of patients (*n* = 12) will be performed as outlined. Healthy volunteers recruited from the staff of our institution will serve as control (*n* = 12).

#### Work package 8 (consecutive sample assessed by full range of fMRI- and EEG-paradigms)

In this work package, we wish to combine all consciousness measures in order to systematically and comprehensively evaluate consciousness in each acute brain injury patient, using the full range of clinical assessments as well as active, passive and resting state fMRI- and EEG-based paradigms. We aim for 24 consecutive TBI and/or non-TBI non-communicating DoC patients admitted to our neurological and neurosurgical ICU or step-down units (inclusion criteria). Prior to inclusion, primary auditory and sensory cortex integrity will be verified using BAEP and SSEP. Exclusion criteria will include those referred to in work package 1.

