#### Exclusion criteria

Exclusion criteria include contraindications for examination by MRI, severe cardiorespiratory compromise and similar acutely life-threatening conditions, evidence of severe pre-morbid neurological deficits such as aphasia or deafness, lack of Danish or English language proficiency, age <15 years, and evidence of defect auditory and sensory pathways [if clinically suspected or as revealed by pretest screening with brainstem auditory evoked potentials (BAEP) and somatosensory evoked potentials (SSEP)]. Sedation is an important confounder during fMRI scans that must be carefully monitored; we will therefore also exclude patients requiring sedation levels exceeding 1 mg/kg/h propofol at baseline. Although we will aim for no sedation or the lowest possible level of sedation to reduce movement artifacts, we will leave the choice of the sedative drug and the dosage to the discretion of the responsible anesthetist. [Fortunately, recent studies indicate that connectivity decreases associated with propofol and sevoflurane sedation, involving the thalamus and insula, are relatively small compared with those already caused by structural brain injury (21, 22)].

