#### fMRI- and EEG-based consciousness paradigms (active, passive, and resting state)

Whereas, active paradigms of consciousness may suggest a higher degree of certainty, passive, and resting state paradigms should also allow detecting signs of consciousness in patients who are not able to cooperate in cognitive tasks because of aphasia, neglect, executive dysfunction, major depression or deafness (1). Indeed, in a recent landmark study, it was shown that intrinsic functional connectivity assessed by fMRI, including (but not limited to) the auditory and default mode networks, may differentiate MCS from VS/UWS at the single-patient level (28). Thus, as stated above, we will establish the full range of fMRI- and EEG-based paradigms, including active, passive, and resting state paradigms.

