## Abbreviations

BAEP: Brainstem auditory evoked potentials
BOLD: blood oxygen level dependent
CRS-R: Coma Recovery Scale-Revised
DRS: Disability Rating Scale
DoC: disorders of consciousness
EEG: electroencephalography
eMCS: emerged from minimal conscious state
FLAIR: fluid attenuation inversion recovery
FOUR: Full Outline of UnResponsiveness
fMRI: functional magnetic resonance imaging
GCS: Glasgow Coma Scale
GOS: Glasgow Outcome Scale
ICU: intensive care unit
MRI: magnetic resonance imaging
MCS: minimal conscious state
mRS: modified Rankin Scale
PI: principal investigator
SSEP: somatosensory evoked potentials
SPIRIT: Standard Protocol Items: Recommendations for Interventional Trials
TBI: traumatic brain injury
UWS: unresponsive wakefulness syndrome
VS: vegetative state
WP: work package.

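### BAEP is credited with verifying auditory cortex although it tests the brainstem, so null results on speech-cued paradigms may be uninterpretable

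*Protocol article*

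**What the plan says.** The article gives the evoked-potential screen a cortical purpose in three places:

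- Work package 8: before inclusion, "primary auditory and sensory cortex integrity will be verified using BAEP and SSEP". This is worded as mandatory.
- Work package 3: patients may have BAEP and SSEP "to ensure intact primary auditory and sensory cortex function". This is optional.
- Work package 6: the same optional tests serve "to confirm primary auditory and sensory cortex integrity".

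Work packages 4 and 7 (active fMRI and active EEG) do not mention the screen.

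The Abbreviations list gives "BAEP: Brainstem auditory evoked potentials". The Exclusion criteria assign the screen a narrower purpose: they exclude patients with "evidence of defect auditory and sensory pathways [if clinically suspected or as revealed by pretest screening with brainstem auditory evoked potentials (BAEP" or SSEP. They also exclude "evidence of severe pre-morbid neurological deficits such as aphasia or deafness", which covers pre-morbid deficits only.

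The section on fMRI- and EEG-based consciousness paradigms expects passive and resting-state paradigms to help "in patients who are not able to cooperate in cognitive tasks because of aphasia, neglect, executive dysfunction, major depression or deafness".

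**The concern.** A brainstem response shows that sound has been carried as far as the brainstem. It does not show that the auditory cortex responds. The target population includes stroke, anoxic-ischemic encephalopathy and traumatic injury, all of which can damage cortex and leave the brainstem auditory pathway intact.

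The paradigms that depend on cortical hearing are central to the study. The passive tasks are "oddball paradigms (“subject's own name,” semantic ambiguity"), and active imagery requires the patient to take in an instruction. The article does not say how instructions are delivered; I assume they are spoken. For a patient without cortical hearing, a null on these tasks says nothing about consciousness.

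Three stated aims are exposed:

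- detecting preserved consciousness, the primary outcome;
- comparing fMRI with EEG, a secondary outcome;
- the hypothesis under Secondary objectives that resting-state connectivity recovers first, passive responses next and command following last.

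The Discussion itself names false-negative evaluations as the main worry.

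**Working it through.** The plan states no figure to reproduce, and the Statistical analysis section declines a power calculation. The check is mainly a comparison of passages.

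**Step 1. What the screen is said to do.**

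| Place | Level claimed |
|---|---|
| Work packages 3, 6 and 8 | Primary auditory and sensory cortex |
| Exclusion criteria | Auditory and sensory pathways |
| Abbreviations (BAEP) | Brainstem |

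For the auditory half, the first row conflicts with the other two.

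**Step 2. Whether anything else closes the gap.** The aphasia and deafness exclusion is pre-morbid only, so deficits from the acute injury are not covered. Exclusion on clinical suspicion covers auditory pathways and gives some protection. Structural MRI is clinically required for every patient (Inclusion criteria), but the article does not use it to judge auditory cortex. No named test checks cortical hearing after the injury.

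**Step 3. What a passing patient without cortical hearing looks like.**

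| Paradigm | Needs cortical hearing | Expected result |
|---|---|---|
| Resting-state fMRI and EEG | No | Can be present |
| Pain, nostril and eye-opening stimuli | No | Can be present |
| Own-name and semantic oddball | Yes | Null whatever the state of consciousness |
| Active imagery (spoken cue assumed) | Yes | Null whatever the state of consciousness |

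- Resting present with oddball and active absent is the pattern of an early stage in the hypothesised recovery order.
- A null on both fMRI and EEG versions of these tasks counts as agreement on absence, yet both nulls share one non-informative cause.

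**Step 4. Illustration of size, under assumptions.** Let f be the share of work package 8 patients who pass BAEP but lack cortical hearing. The article gives no value, so I take 0 to 30%. Suppose that such patients are scored negative, that the background command-following rate is 15% (Introduction), and that covert command following is equally common with and without cortical hearing. Then the apparent rate is 0.15 × (1 − f), expected positives are 24 × that rate, and uninformative patients number 24 × f.

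| f | Apparent rate | Expected positives of 24 | Uninformative patients |
|---|---|---|---|
| 0% | 15.0% | 3.60 | 0 |
| 10% | 13.5% | 3.24 | 2.4 |
| 20% | 12.0% | 2.88 | 4.8 |
| 30% | 10.5% | 2.52 | 7.2 |

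The table shows direction only. The 15% refers to patients with a clinical vegetative-state diagnosis, and the article says that such paradigms were typically tested in chronic injury. This study enrols acute and sub-acute patients, with diagnoses from coma to locked-in syndrome.

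**The case against.** The strongest reply is that the fault is one of wording. Four parts of it have force.

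- **Scoring.** A reader might infer that patients without cortical hearing are recorded as negative for consciousness. The article does not say so. It gives no coding rule in either direction, and one may stand in the full protocol or analysis plan, neither of which is shown. Only the weaker statement holds: a null can be read as negative.
- **Other evidence.** The primary outcome also rests on clinical evaluation and resting-state connectivity, and a composite reference standard is proposed. The article relies on passive and resting-state paradigms for patients who cannot cooperate. A null on a speech-cued task is therefore not the study's verdict on consciousness. This stands, except that the oddball tasks, although passive, cannot help a patient who does not process the sound.
- **The sensory half.** A reader might take the whole screen to be invalid. Nothing in the documents shows SSEP to be unsuitable for sensory cortex.
- **The remedy.** Cortical activation and evoked potentials in passive runs are themselves outcome measures. Using them to decide who counts would turn an outcome into an entry filter and build part of the recovery order into the analysis. This is right, and it limits the fix to a flag with parallel reporting.

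The Discussion also says that paradigm results reach attending clinicians only after the relevant work packages are complete, although a summary may be shared on request. This reduces the immediate clinical consequence but not the analytic one.

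The reply does not remove the conflict on the page. The mandatory screen in work package 8, followed exactly, does not deliver the property claimed for it.

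**Conclusion.** The point holds in a limited form. The claim that BAEP ensures, confirms or verifies primary auditory cortex in work packages 3, 6 and 8 is wrong by the article's own definition and inconsistent with its exclusion criteria. Patients with injured auditory cortex can enter work package 8, and their nulls on own-name, semantic-ambiguity and spoken-command tasks are then uninterpretable.

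The bias would run towards a lower detection rate and more apparent fMRI/EEG agreement on absence. Its size cannot be derived from the document: it depends on an unknown share of patients and an unseen scoring rule. In the illustration, even a 30% share costs about one expected positive (3.60 − 2.52 = 1.08), but 7.2 of 24 patients would carry no information on these tasks.

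Intact primary auditory cortex would still not establish speech comprehension, so a correct cortical check removes only part of the ambiguity.

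**What to change.** 1. In work packages 3, 6 and 8, restate BAEP as a check of the auditory pathway to the brainstem, in line with the Exclusion criteria. Leave the SSEP statement as it is.
2. In work packages 3, 6 and 8, where passive runs are planned, define a low-level cortical response to sound (for example an early cortical auditory component on EEG, or sound against silence on fMRI). Read it with the clinical structural MRI. Do not use the oddball effect. Where the response is missing, flag auditory-cued results as not evaluable.
3. Keep all patients enrolled and in the resting-state analysis. Report detection on auditory paradigms, and fMRI/EEG agreement, for all enrolled and for evaluable patients side by side.
4. Keep the all-enrolled result for the recovery-order hypothesis, because passive responses are outcomes there.
5. Work packages 4 and 7 describe no passive run. Use structural MRI alone there, or state the limitation.

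The wording change costs nothing. The rest needs no new procedure in work packages 3, 6 and 8, provided that the passive fMRI run contains silent periods, which the article does not state. The price is a smaller evaluable denominator, in samples of 12 and 24, and a little more analysis.

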#### Work package 9 (full clinical service)

Once we have shown that comprehensive fMRI- and EEG-based consciousness paradigms are feasible in patients with acute brain injury in the ICU and intermediate care units, we wish to establish a full clinical service and a national referral center for the evaluation of DoC patients following acute brain injury. This will lay the foundation for a fruitful research environment (phase 3).

If necessary, amendments to the work packages will be published on clinicaltrials.org (NCT02644265).

### Statistical analysis

A power calculation of the required sample size that would include the combined different methods does not appear feasible owing to the multimodal design of CONNECT-ME but the numbers of patients recruited into the different work packages reflects empirical numbers derived from previous results on consciousness paradigms in the critical care setting (21, 47). In addition to descriptive statistics, we will perform correlation analysis between behavioral scales (CRS-R total score) and default mode networks, respectively, EEG entropy using Spearman testing. Non-parametric tests will be used for univariate analysis (Wilcoxon rank sum/Mann-Whitney test and Kruskal-Wallis test) to test whether default mode and other brain networks or EEG entropy differ between diagnostic groups (VS/UWS vs. MCS). Machine learning models will be applied to evaluate resting-state fMRI and other neuroimaging measures as predictors of covert consciousness and subsequent recovery (i.e., does imaging data inform patient level of consciousness and/or prognosis). Receiver operating characteristic (ROC) analysis may be used to identify a cut-off value differentiating conscious (MCS) from unconscious (coma or VS/UWS) patients. Results will be considered significant at *p* < 0.05 or lower, if appropriate (e.g., <0.001 for fMRI data). Statistical advice and supervision, including exploration with advanced machine learning algorithms, will be provided in-house (Department of Biomedical Statistics, University of Copenhagen).

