#### Secondary objectives

We wish to pool fMRI- and EEG-based data as well as results from systematic clinical evaluations and genomic and metabolomic data to study the neuronal mechanisms by which patients regain consciousness following acute brain injury.

We will test the following hypotheses:
fMRI- and EEG-based consciousness paradigms are feasible in patients with complete (or near-complete) loss of motor function in the acute phase of brain injury.fMRI- and EEG-based consciousness paradigms, including state-of-the-art clinical rating scales and bedside techniques such as pupillometry, applied in the acute phase of brain injury, will add clinically relevant information that complements standard bedside examination. This includes detection of preserved consciousness in some patients who were clinically classified as being unconscious due to lost motor output.fMRI- and EEG-based consciousness paradigms do not always yield the same evidence for the presence or absence of consciousness in acute brain injury.Serial multimodal evaluations will better reflect a changing level of consciousness than single unimodal assessments.In most patients who regain consciousness after acute brain injury, the following pattern will be observed: Intrinsic cortical connectivity, including fronto-parietal networks, as revealed by resting state paradigms will recover first, followed by the occurrence of cognitive evoked potentials and cortical activation (passive paradigms), and lastly, the ability to follow commands (active paradigms).Because of the absence of a gold standard for consciousness (1), a composite reference standard, considering bedside examination, clinical rating scales and fMRI- and EEG-based consciousness paradigms, allows the most reliable classification of patients with DoC (16).Genomic and metabolomic data may reveal signatures for consciousness recovery.

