##### fMRI

Resting-state fMRI are performed on a 3T Prisma MRI scanner with 64-channel head coil. Despite altered states of consciousness, participants are instructed to close their eyes and let their mind wander, but not to fall asleep. During the procedure, patients are monitored by an experienced neuroanesthesiologist and a nurse anesthetist; patients are sedated, if necessary, with sevoflurane or propofol at low doses for optimal image acquisition and mechanically ventilated aiming at normal ventilation. Participants complete a 10-min T2^*^-weighted echo-planar imaging BOLD fMRI sequence (no. of volumes = 300 volumes, TR/TE = 2,000/30 ms, flip angle = 90°, in-plane matrix 64 × 64, number of slices = 32, voxel size = 3.6 × 3.6 × 3.75 mm). A high-resolution 3D T1- weighted structural image is acquired using a sagittal, magnetization prepared rapid gradient echo (MP-RAGE) sequence (TR/TE/TI = 1,900/2.58/900 ms, flip angle = 9°, in-plane matrix 256 × 256, number of slices = 224, voxel size = 0.9 × 0.9 × 0.9 mm). We use single-subject seed-based analysis to estimate seed-to-voxel and seed-to-seed connectivity. Functional imaging data are pre-processed using SPM12 (https://www.fil.ion.ucl.ac.uk/spm/software/spm12/) and Conn v16.b (29). We will visually inspect all acquired scans to assess data quality and document morphological abnormalities that may introduce noise. We account for physiological and other noise sources using methods typically applied to resting-state fMRI data. This includes applying a bandpass filter (range 0.008–0.09 Hz) and denoising gray-matter voxel time series using aCompCor (30). We will quantify default-mode network and other canonical resting-state networks using regions defined from an independent dataset (e.g., “networks” region set in Conn). We use Fisher's r-to-z transformation to convert the estimated correlation coefficient (rho) between any of two means, denoised time series. Qualitative assessment of the presence of DMN (21) and other networks will be complemented by data-driven strategies, including defining deviation from normal DMN connectivity defined as a multivariate distribution based on a reference healthy control population that has been scanned on the same MRI using scan parameters identical to those we use here (31). Investigators classifying the DMN are blinded to clinical outcome.

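### The rank tests relating default mode connectivity to CRS-R and diagnostic group are unadjusted for sedation at the scan, which the protocol itself names as a confounder; the direction and size of the bias are unknown

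*Protocol article*

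**What the plan says.** The Statistical analysis section of the Protocol article fixes two kinds of test for the relation between brain measures and level of consciousness. The first is a rank correlation: "we will perform correlation analysis between behavioral scales (CRS-R total score) and default mode networks, respectively, EEG entropy using Spearman testing". The second compares VS/UWS with MCS: "Non-parametric tests will be used for univariate analysis (Wilcoxon rank sum/Mann-Whitney test and Kruskal-Wallis test"). Significance is set at p below "0.05 or lower, if appropriate (e.g., <0.001 for fMRI data"). No covariate, stratum or sensitivity analysis is named for either.

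Elsewhere the article treats sedation as a threat to these same measurements. Exclusion criteria: "Sedation is an important confounder during fMRI scans that must be carefully monitored". That section excludes patients who need propofol above 1 mg/kg/h at baseline, then leaves drug and dosage to the responsible anesthetist. The fMRI part of work package 1 adds: "patients are sedated, if necessary, with sevoflurane or propofol at low doses for optimal image acquisition". Work package 2 lists sedation among the target data: "cause of admission, sedation, surgical and non-surgical complications".

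On timing, the section on bedside examination has patients rated within 30 minutes before and after each fMRI and EEG session (60 minutes in work package 4). The EEG is recorded with "video observations within 1 h before or after fMRI (or as close to this time as possible").

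**The concern.** The protocol names a confounder, allows it to vary between patients at the moment of measurement and records it, but then chooses tests with no place for it. A plain Spearman correlation or a univariate rank test compares sedated and unsedated scans as if they were alike.

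The bias does not require sedation to change the CRS-R score. It is enough that sedation lowers connectivity and that the chance of being sedated is related to CRS-R. Both directions are plausible. The article ties sedation to movement artifacts and image quality, which would point to patients who move more. It also foresees patients who cannot be weaned from sedation, who may score lower.

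A second route is timing. Each session has a CRS-R rating before and one after it, and the analysis section does not say which one enters the test. A rating made after scan sedation could share the sedation effect with the scan.

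At stake is whether an association, or its absence, in 12 to 24 patients reflects consciousness or who was sedated.

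**Working it through.** There is no figure in the plan to reproduce. The article says a power calculation was not feasible and gives no expected correlation, share sedated or sedation effect. All inputs below except the sample sizes and the 0.05 level are therefore assumptions.

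**Inputs.** Sample sizes: 24 (work packages 1 and 8) and 12 (work packages 3, 4, 6 and 7). Two-sided 5% level (sidedness is not stated). Assumed: Pearson correlation 0.50 between latent CRS-R (x) and connectivity (y); sedation s given with probability p_high in the upper CRS-R half and p_low in the lower half; sedation lowers connectivity by d SD, so the observed value is y - d*s.

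**Step 1: no sedation.** Spearman = (6/pi) * arcsin(0.50/2) = 0.483.

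**Step 2: unadjusted Spearman with sedation** (simulation, 400,000 draws).

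| p_high / p_low | d = 0.5 | d = 1.0 |
|---|---|---|
| 60% / 10% | 0.38 | 0.26 |
| 10% / 60% | 0.55 | 0.59 |
| 40% / 30% | 0.45 | not used |
| 30% / 40% | 0.49 | not used |

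The sign of the error follows the assumed split. With a near-even split and d = 0.5 the value stays within about 0.03 of 0.48.

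**Step 3: what this means at n = 24.** The critical rank correlation at 5% is about 0.404 (0.576 at n = 12). By Fisher's z, the standard error is sqrt(1.06/(24-3)) = 0.225.
- No sedation: atanh(0.483)/0.225 = 2.35, power about 65%.
- 60%/10%, d = 0.5: atanh(0.38)/0.225 = 1.78, power about 43%.
- 60%/10%, d = 1.0: atanh(0.257)/0.225 = 1.17, power about 22%.

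**Step 4: does adjustment help?** Partial Spearman = (r_xy - r_xs*r_ys) / sqrt((1 - r_xs^2)(1 - r_ys^2)), on ranks, with components from the same simulation.
- 60%/10%, d = 1.0: (0.256 + 0.456*0.260) / sqrt((1 - 0.208)(1 - 0.068)) = 0.375/0.859 = 0.44.
- 10%/60%, d = 1.0: (0.593 - 0.456*0.583) / sqrt((1 - 0.208)(1 - 0.340)) = 0.327/0.723 = 0.45.

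The unadjusted values are 0.26 and 0.59; the adjusted ones agree. They lie slightly below 0.48 because adjusting for a correlate of CRS-R removes some of its spread.

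**Step 5: false positives if sedation lowers both measures.** Simulation with no true association, one session per patient, 30-50% sedated. With a shift of 0.25-0.5 SD in both measures, the unadjusted Spearman test rejects in 4.5-5.9% of runs, which is no practical harm. With 1 SD it rejects in 8.4-9.0% (n = 12) and 12.8-16.1% (n = 24). The sedation-adjusted test stays at 4.1-6.2%.

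**The case against.** **The article does not ignore sedation.** It excludes patients above a baseline propofol level, aims for none or the lowest possible level, scans only once sedation is stopped or reduced (Discussion), and records sedation. It also describes sedation-related connectivity decreases as relatively small compared with those from structural injury. This stands in part: the controls narrow the range of sedation, and Step 5 shows little harm at small effects. But the numerical limit covers propofol at baseline, not sevoflurane or sedation given for the scan. And the comparison with structural injury does not settle a contrast in which both groups have injured brains.

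**A condensed article may leave covariates to a fuller plan.** This is a fair point on missing detail. Here, however, the tests are named, and those for group comparison are called univariate. The point concerns a stated method.

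**Stronger readings that the document does not support.**
- A reader might infer that serial sessions are treated as independent, because serial assessment is a stated hypothesis ("Serial multimodal evaluations will better reflect a changing level of consciousness than single unimodal assessments"). The analysis section never says that sessions are pooled, and no session count is given. Pooling would matter: with 3 sessions in each of 24 patients and a within-patient correlation of 0.3-0.8, the Spearman test rejects a true null in 6.6-19.7% of runs. With one session per patient there is no inflation (3.9-5.4% across Spearman and Mann-Whitney).
- A reader might take these as the main tests. The article lists the correlations with clinical data under secondary outcomes.
- A reader might conclude that sedation masks the association. That needs sedation to go mainly to patients with higher CRS-R, which the document does not state; the reverse split exaggerates the association.
- The confounder statement is about fMRI. Extending it to EEG entropy is an inference, reasonable only where the EEG was recorded under or after scan sedation.

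**Conclusion.** The point holds for the fMRI analyses: the stated rank tests do not adjust for a confounder that the protocol names, allows to vary at the scan and records. Design measures reduce the bias without removing it.

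Its direction and size are unknown. Under the assumptions above, an underlying correlation of 0.48 could appear as anything from 0.26 to 0.59, or almost unchanged if sedation is nearly unrelated to CRS-R and its effect is 0.5 SD. That range rests on an assumed effect of 0.5-1.0 SD and on splits of up to 60% against 10%, neither of which comes from the document. The finding is therefore that the result could not be interpreted cleanly, not that it would be wrong in a known direction. A change is worthwhile because it is cheap and the samples are small.

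**What to change.** In the Statistical analysis section, for the fMRI analyses:

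1. Use one session per patient, chosen by a stated rule, with the CRS-R rated before the scan. The examination schedule already provides that rating.
2. Report a partial Spearman correlation of CRS-R with connectivity, adjusted for sedation at acquisition (yes/no).
3. Compare VS/UWS with MCS by a method adjusted for or stratified by the same variable, for example a stratified Wilcoxon (van Elteren) test.
4. Add a sensitivity analysis restricted to unsedated scans.
5. Do the same for EEG entropy where the EEG was recorded under or after scan sedation. The EEG need not be re-timed.
6. If several sessions per patient enter one test, account for clustering by a random patient effect or by resampling patients.

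Cost: about one degree of freedom for the adjustment. The sensitivity analysis is smaller: if 35% were sedated (the mean of 60% and 10%), 24 * 0.65 = about 16 patients would remain. A stratum containing only one diagnostic group adds nothing to a stratified test. The sponsor must confirm that sedation is recorded per session, because the database description lists only sedation in general. A larger model with agent, time since injury and within-patient terms is not asked for; 12 to 24 patients would not carry it well.
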